**4.3.2. TEST-RETEST RELIABILITY (INTRA-PATIENT)**
To evaluate electrophysiological reliability, measurements will be repeated 6 times (2 per visit, across 3 visits within one month).
A trained operator (same in each center) will perform all electrophysiological tests using standardized equipment identical across visits.

Indicators for intra-patient (6 repeated measures), intra-visit (2 repeated measures), or inter-visit (3 repeated measures) reliability will include:

- Bland-Altman plots describing the differences between repeated measures vs. their mean. This visually evaluates absolute differences, systematic bias, bias variation, and variance of differences. Mean systematic bias (average difference) with 95% CI and 95% limits of agreement will be estimated (Bland & Altman, 1999).
- Intraclass correlation coefficients (ICC) for intra-patient, intra-visit, and inter-visit reliability.

**4.3.3. PSYCHOMETRIC EVALUATION OF THE NAERT QUESTIONNAIRE**
Using the French-translated scale, the following properties will be assessed:

- Internal consistency (Cronbach’s alpha coefficient),
- Inter-item and total-item correlation coefficients,
- Factor analysis to evaluate unidimensionality,
- Test-retest reliability across 3 repeated measures (one per visit, in clinically stable conditions) using Bland-Altman method and ICC calculation.

**5. STUDY DESIGN**

**5.1. JUSTIFICATION OF METHODOLOGICAL CHOICES**
In this study, the objective is to evaluate the validity and reliability of various electrophysiological parameters to better and objectively identify the severity of symptom impact in SCD.

The reliability of a measurement sets the upper limit of the maximum validity it can achieve (Streiner, 2015). The methodological choices made to address the objectives are as follows:

- Selection of patients with unilateral SCD formally diagnosed by temporal bone CT: patients with bilateral SCD will not be included to avoid uncertainty in attributing symptoms to one, the other, or both SCDs.
- No requirement for symptom severity, to obtain a population sufficiently heterogeneous in terms of symptom impact and representative of patients followed in ENT hospital services.
- Stable SCD in a diagnostic and follow-up context, with no therapeutic intervention planned within 3 months of the first visit. This allows evaluation of the test-retest reliability of different electrophysiological parameters, with measurements repeated over 3 successive visits (less than one month apart) and 2 repeated measurements at each visit. These repeated measures will allow assessment of intra-patient reliability (6 repeated measurements), intra-visit reliability (2 repeated measurements per visit), and inter-visit reliability (3 repeated visits).

The evaluation of the validity of electrophysiological measurements will primarily rely on a convergent and divergent validation approach by estimating the associations between each electrophysiological parameter and patient-reported symptoms (cardinal symptoms, Naert questionnaire, and quality of life). The main hypothesis (based on the theoretical model from the literature) is that the SP/AP ratio measured in electrocochleography will be the parameter most strongly correlated with the cardinal symptoms, compared to other electrophysiological parameters. More generally, all correlations obtained in this study between clinical and paraclinical measures will provide a better understanding of the construct validity of the various electrophysiological parameters.

The Naert questionnaire is not yet validated in French. A translation of the scale is underway, and the psychometric properties of this new translated version will be evaluated during this study. Repeated administration of the questionnaire over the 3 follow-up visits will allow assessment of test-retest reliability.

The Naert questionnaire translation follows the recommendations described by Hall et al. (2017). The corresponding author ([name]) has authorized the use of this questionnaire in our study. The translation from English to French was performed by two bilingual translators with French as their native language (one professional translator, one healthcare professional), and an intermediate French version of the questionnaire was harmonized. This intermediate version is currently undergoing back-translation by a third bilingual translator with French as their native language, and corrections will be made if discrepancies are significant.

A review committee including two SCD expert clinicians (Dr [name], Prof. [name]), the three translators, and an expert patient with SCD will be convened to validate the version to be tested in the field. This version will be submitted to a group of 8–10 SCD patients, representative of the symptomatic variability observed in practice, to assess comprehension and ease of completion and to finalize a validated questionnaire before study initiation. The formal validation study of the final translated version will then be conducted on the 100 patients included in this project, with evaluation of its psychometric properties.

**5.2. STUDY SCHEMA**
Cohort study of patients with unilateral SCD diagnosed by CT,

- prospective,
- national, multicenter,
- descriptive of clinical and paraclinical characteristics of the pathology and their correlations.

Evaluation of the reliability of electrophysiological parameters relies on repeated measurements:

- across 3 visits (less than one month apart),
- two repeated measurements per visit, following standardized procedures on standardized equipment, performed by a single trained operator at each center.

Test-retest reliability of the Naert questionnaire (French translated version) is based on repeated measurements across 3 successive visits (less than one month apart).

**5.3. RANDOMIZATION METHODS**
No randomization procedure is planned in this study.

**6. ELIGIBILITY CRITERIA**

**6.1. INCLUSION CRITERIA**

- Unilateral SCD formally diagnosed by high-resolution CT (≤0.5 mm slices, reconstructions in the plane of the superior semicircular canal and perpendicular plane) of the temporal bone, with no requirement for symptom severity.
- If present, SCD-related symptoms must be stable in a diagnostic and follow-up context, with no therapeutic intervention planned within 3 months of the first visit.
- Adult patient (≥18 years), able to read and understand French.
- Affiliated with or beneficiary of a social security scheme.
- Free, informed, written consent signed by the participant and investigator (at the latest on the day of inclusion and before any study-related examination).

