**2.1.2.1 Vestibular Evoked Myogenic Potentials (VEMPs)**
VEMPs assess the function of the two otolith organs in the vestibule: the utricle and saccule. Utricular function is assessed by ocular VEMPs via the utriculo-ocular pathway, using short high-intensity auditory stimuli (500 Hz and/or 2000 Hz tones at 90 dB SPL) delivered via headphones to the test ear and recorded with a surface electrode under the contralateral lower eyelid. Saccular function is assessed by the cervico-collic reflex, with inhibitory muscular responses recorded from the ipsilateral sternocleidomastoid.

In unilateral SCD, VEMP thresholds (ocular and cervical) are lowered and amplitudes increased compared to the unaffected ear, reflecting vestibular hyper-reflexivity. VEMP sensitivity and specificity in SCD diagnosis exceed 70% (Hunter et al., 2017; Noij et al., 2020). Some authors have proposed combining VEMPs with low-frequency conductive hearing loss as a “third window indicator” with 92% sensitivity and 100% specificity (Noij et al., 2018).

VEMP abnormalities can aid SCD diagnosis, especially in ambiguous CT cases, but do not correlate with symptom type or severity (Bae JS et al., 2013; Noij et al., 2018). No standardized thresholds exist, and post-surgical VEMP interpretation can be challenging due to utricular or saccular deficits.

**Figure 2:** Example of cervical VEMPs with abnormal lowered thresholds on the left side.

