**2.1.2.3 Electrocochleography (EcoG)**
EcoG non-invasively records inner ear responses using a tympanic electrode. Key measures include the summating potential (SP) from hair cells and action potential (AP) from auditory neurons, with the SP/AP ratio often analyzed. SP/AP may increase in hair cell polarization anomalies, as seen in Ménière’s disease. Inner ear biomechanical changes in SCD may also elevate SP/AP.

Recent studies (Park et al., 2015; Wenzel et al., 2015; Adams et al., 2011) indicate EcoG as a promising objective marker of SCD symptom impact, with SP/AP decreasing post-surgical canal occlusion in symptomatic patients, correlating with clinical improvement. Normal SP/AP values are consensus-defined (<0.25 at >70 dB SPL, <0.35 at 40–70 dB SPL).

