**4.2.2. CT SCAN**
Formal evidence of SCD is a main inclusion criterion. Temporal bone CT is performed before inclusion using high-resolution scans (≤0.5 mm slices), with reconstructions in the plane of the superior semicircular canal and its perpendicular plane (see Figure 5).

*Figure 5: Reconstructions of the superior semicircular canal and perpendicular plane confirming SCD*

SCD is characterized by loss of bone hyperdensity over at least two consecutive slices (Lookabaugh et al., 2015). Its location (anterior limb, arch, posterior limb), largest dimension in mm, and surface area in mm² are recorded.

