**6.2. EXCLUSION CRITERIA**

- Bilateral SCD diagnosed by high-resolution temporal bone CT, to avoid uncertainty in symptom attribution.
- Doubtful SCD diagnosis on high-resolution temporal bone CT (uncertainty regarding bone discontinuity, technical characteristics of the scan, or absence of specific reconstructions).
- Associated otologic or otoneurological pathology that could cause symptom impact similar to SCD: chronic otitis media, Eustachian tube dysfunction, otosclerosis and other ossicular anomalies with normal tympanum, definite Ménière’s disease, vestibular migraine.
- Patient under judicial protection or other protective regime (guardianship, curatorship).
- Pregnant women.

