**8.1.2. OTHER TREATMENTS/PROCEDURES**
Patients may continue any treatments initiated prior to the start of the study.

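### The eligibility criteria do not exclude ears already operated on for SCD, although the protocol itself says surgery lowers SP/AP together with symptoms and complicates VEMP interpretation

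*Protocol*

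**What the plan says.** **Eligibility.** Protocol section 6.1 asks for CT-confirmed unilateral SCD "with no requirement for symptom severity". Where symptoms exist, "SCD-related symptoms must be stable in a diagnostic and follow-up context", "with no therapeutic intervention planned within 3 months of the first visit". The ear-related exclusions in section 6.2 are bilateral SCD, a doubtful CT, and "Associated otologic or otoneurological pathology that could cause symptom impact similar to SCD". Previous SCD surgery appears in neither list, nor in the criteria in the section 1 summary and the English abstract. Section 8.2 forbids SCD intervention only while the patient is in the study.

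**Qualifying scan.** Section 4.2.2 says "Temporal bone CT is performed before inclusion using high-resolution scans", and section 9.3.2 has that existing scan re-examined at pre-inclusion. No maximum age is set, and nothing requires the scan to be later than any surgery.

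**Effect of surgery.** Section 2.1.2.3 describes EcoG as promising, "with SP/AP decreasing post-surgical canal occlusion in symptomatic patients, correlating with clinical improvement"; the section 1 summary says the same. Section 2.1.2.1 adds that "post-surgical VEMP interpretation can be challenging due to utricular or saccular deficits". Section 2.1.1 puts insufficient improvement after surgery at 10-30%.

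**Analysis.** Section 11.2 correlates SCD-side indicators with symptoms over all patients and mentions no separation by earlier surgery. Section 4.3.1 expects a significant positive SP/AP correlation that is higher than the one for VEMP.

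**The concern.** The primary objective asks whether SP/AP tracks symptom severity in an ear with a dehiscence. By the protocol's own account, surgery moves both variables of that correlation in the same direction. A successfully operated ear has low SP/AP and low VAS because it was treated. A group of such ears yields a positive pooled correlation even if SP/AP carries no information among untreated ears, and inflates a correlation that does exist.

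The comparison between markers is exposed too. Utricular or saccular deficits after surgery disturb VEMP, which can lower its correlation with symptoms. That favours the hypothesis in sections 2.2 and 5.1 that EcoG is the strongest marker.

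The setting makes entry plausible. Section 6.3 recruits from consultations at centres chosen for their experience in managing SCD, section 6.1 covers follow-up as well as diagnosis, and no symptom level is required, so a patient relieved by surgery is not screened out.

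**Working it through.** **1. The plan's own precision figures (section 11.1, n = 100).** Fisher z interval, with 1.96/√97 = 0.199:
- r = 0.50: tanh(0.549 ± 0.199) = 0.337 to 0.634, width 0.297, as stated (below 0.30).
- r = 0: ±0.196, width 0.393, as stated (below 0.40).

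Both reproduce. They describe sampling error only. Confounding by surgery is a bias, which a larger sample does not remove.

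**2. Inputs not in the document (assumed).** Share operated p = 10, 20, 30%. Fall in operated ears: d₁ = 1.0 to 1.4 SD in SP/AP, d₂ = 1 SD in VAS. SDs are within group.

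**3. Spurious correlation, true r = 0 within each group.** Pooled r = p(1−p)d₁d₂ / √[(1 + p(1−p)d₁²)(1 + p(1−p)d₂²)].

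| p | p(1−p) | d₁ = 1.0 | d₁ = 1.4 |
|---|---|---|---|
| 10% | 0.09 | 0.09/1.09 = 0.083 | 0.126/√(1.1764 × 1.09) = 0.111 |
| 20% | 0.16 | 0.16/1.16 = 0.138 | 0.224/√(1.3136 × 1.16) = 0.181 |
| 30% | 0.21 | 0.21/1.21 = 0.174 | 0.294/√(1.4116 × 1.21) = 0.225 |

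The two-sided 5% critical value at n = 100 is r = 0.197, so one of the six cells exceeds it. The others still raise the chance of a nominally significant positive result, which is 2.5% when r is truly 0. With d₁ = d₂ = 1, Φ(atanh(r)·√97 − 1.96) gives about 13%, 28% and 41%.

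The result depends on the assumed shift. With 1.5 SD on both measures, pooled r is 0.168, 0.265 and 0.321.

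**4. Inflation, true r = 0.50, both measures lower by 1 SD.** (0.50 + 0.09)/1.09 = 0.541; (0.50 + 0.16)/1.16 = 0.569; (0.50 + 0.21)/1.21 = 0.587.

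**5. Masking by failed surgery, true r = 0.50.** Assume SP/AP falls 1.4 SD with no symptom relief. Section 2.1.1 puts failures at 10-30% of operated patients, so with 10-30% operated they make up 0.10 × 0.10 = 1% to 0.30 × 0.30 = 9% of the sample. Pooled r = 0.50/√(1 + p(1−p) × 1.4²), considering failures alone:
- 1%: 0.50/√(1 + 0.0099 × 1.96) = 0.495.
- 9%: 0.50/√(1 + 0.0819 × 1.96) = 0.464.

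Successful operations in the same sample push the other way, as in step 4.

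**The case against.** The sponsor may well intend unoperated patients only. Section 4.2.2 requires the bone to be missing on at least two adjacent slices, section 6.2 removes any doubtful defect, and section 9.3.2 has the scan checked again. A repaired canal on a recent scan could fail these tests. Section 12.3 provides for coded medical history in the eCRF, and an analysis plan that is not shown could separate operated ears.

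Part of this stands: the CT rule is a partial safeguard and the intention may be sound. But the scan may predate the operation, follow-up can as easily mean post-operative follow-up, and five centres could read the criteria differently. Who is eligible is a matter for the protocol, not the analysis plan.

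Four stronger readings are tempting and not supported:
- A reader might infer that a patient with bilateral SCD, operated on one side, could enter as unilateral. Section 6.2 excludes bilateral SCD diagnosed on CT and does not limit this to the latest scan.
- A reader might take section 8.1.2, "Patients may continue any treatments initiated prior to the start of the study", as admitting operated ears. It concerns ongoing treatment; a completed operation is not something one continues.
- A reader might infer heavy masking, with r of 0.50 falling to 0.46, 0.44 and 0.42. Those values need every operated ear to be a failure, against the 10-30% in section 2.1.1.
- A reader might want all middle or inner ear surgery excluded. The statements in the protocol on SP/AP and VEMP after surgery concern SCD surgery only.

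**Conclusion.** The point holds as a gap in the eligibility criteria with a confounding mechanism that the protocol itself describes. As written, ears operated on for SCD can enter, and section 11.2 pools them with untreated ears. The likelier distortion is a created or inflated SP/AP-symptom correlation, together with a weakened VEMP comparator; masking by failed surgery is small.

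The size is not known. It rests on an operated share and SD shifts that the document does not give, so the figures above are illustrations. At shifts of 1.0 to 1.4 SD in SP/AP and 1 SD in VAS, the spurious r is at most 0.225. That can reach nominal significance but falls well short of the r of 0.50 used for precision in section 11.1. It would therefore be wrong to infer that the study must return a false strong association, or that operated patients have in fact been enrolled. The absence of the criterion is certain; its numerical effect is not.

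**What to change.** Add one exclusion to section 6.2, and repeat it in the section 1 summary and the abstract: *previous surgery for SCD on either ear*. Either ear is meant because the opposite ear is the divergent-validity control and the reference for VEMP amplitude (section 4.2.1.3). State also that the qualifying CT must show an unoperated ear.

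If operated patients are already enrolled, record earlier SCD surgery by ear in the eCRF and leave these patients out of the primary validity correlations. They can stay in the reliability analyses, which compare each patient's repeated measures with one another.

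The cost is an amendment of one line and one eCRF item, plus some loss of eligible follow-up patients. That loss cannot be sized: section 6.3 counts patients consulting for SCD, not how many have been operated on. The precision in section 11.1 is unchanged provided 100 unoperated patients are still recruited; if enrolled patients are set aside from the validity correlations, the intervals there widen accordingly.

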**6.2. EXCLUSION CRITERIA**

- Bilateral SCD diagnosed by high-resolution temporal bone CT, to avoid uncertainty in symptom attribution.
- Doubtful SCD diagnosis on high-resolution temporal bone CT (uncertainty regarding bone discontinuity, technical characteristics of the scan, or absence of specific reconstructions).
- Associated otologic or otoneurological pathology that could cause symptom impact similar to SCD: chronic otitis media, Eustachian tube dysfunction, otosclerosis and other ossicular anomalies with normal tympanum, definite Ménière’s disease, vestibular migraine.
- Patient under judicial protection or other protective regime (guardianship, curatorship).
- Pregnant women.

**6.3. FEASIBILITY AND RECRUITMENT MODALITIES**
Lyon, Bordeaux, and Toulouse are the three French centers with the most clinical experience in SCD management nationally and in related scientific publications.
The number of patients consulting for SCD exceeds 40/year in Lyon, Bordeaux, Montpellier, and Toulouse, and about 10/year at the University Hospital of La Réunion. [name] is the reference specialist in otology and otoneurology at CHU Saint-Denis, with specialized responsibilities for cochlear implants and complex otoneurological pathologies. Participants will be recruited during their consultations. General ENT correspondents at each center will be informed of the study and may refer eligible patients to their respective study center. Recruitment may also be facilitated by neuroradiology teams associated with each center, who make the radiological SCD diagnosis and can inform patients about the study.
Each of the 5 investigating centers is a nationally or internationally recognized expert center in otoneurology and functional hearing and balance assessments.

**7. STUDY TREATMENT/STRATEGY/PROCEDURES**

**7.1. EXPERIMENTAL TREATMENT/STRATEGY/PROCEDURE**
This study aims to correlate objective anomalies present in SCD at the electrophysiological or radiological level with SCD symptom severity. High-resolution temporal bone CT will have been performed prior to the study and will serve as an inclusion criterion. The electrophysiological assessments in this study are non-invasive and routinely used in otoneurology consultations. No adverse effects are expected beyond discomfort from the probe in the external auditory canal and/or loud sound delivery.

- **EcoG**: records cochlear and neural responses via an electrode near the tympanum to controlled auditory stimulation delivered via headphones.
- **WBT**: measures acoustic energy absorbed by the tympano-ossicular system using a tympanometry probe inserted in the external auditory canal delivering wideband sounds.
- **PEMV recording**: measures muscular responses to high-intensity auditory stimulation delivered via headphones using electrodes on the neck or lower eyelid.

**7.2. COMPARISON TREATMENT/STRATEGY/PROCEDURE**
Not applicable.

**7.3. PRODUCT CIRCUIT**
Not applicable.

**7.4. BLINDING**
Not applicable.

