**4.2.1.1. ELECTROCOCHLEOGRAPHY**
Two EcoG measurements are performed at each of the three planned visits, recording summation potential (SP) and action potential (AP) at each measurement (see Figure 3). The SP/AP ratio is calculated for each of the 6 measurements, as well as an average SP/AP ratio per visit and an overall average across all 6 measurements.

*Figure 3: Electrode placement and typical EcoG recording (from Interacoustics Academy)*

All recordings are performed by the same examiner within one center using the EcoG module of the Eclipse® modular system by Interacoustics®.

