**4.2.1.3. PEMV**
Two ocular and cervical PEMV recordings are performed at each of the three visits, collecting the PEMV threshold (dB SPL) and wave amplitude characterization relative to the contralateral healthy side (absent, normal, or abnormally large). PEMV thresholds and the proportion of abnormally large PEMV across the 6 measurements are recorded.

All recordings are performed by the same examiner within one center using the EcoG module of the Eclipse® system (Interacoustics®).

In each center, the examiner responsible for electrophysiological assessments will have received standardized training by [name] (Associate Professor, University Clermont-Auvergne, and consultant to Interacoustics®).

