**9.3.2. VISIT PROCEDURE**
The pre-inclusion/inclusion visit is conducted by the investigator. Before any study-related examination, the investigator obtains free, informed, written consent from the participant (or legal representative, if applicable).

At the pre-inclusion visit, the previously performed temporal bone CT will be examined to formally confirm the SCD diagnosis.

At the inclusion visit, the following will be performed:

- Clinical examination and evaluation of cardinal symptoms (pulsatile tinnitus, autophony, sound-induced balance disorders, pressure-induced balance disorders)
- Naert questionnaire
- Electrophysiological measurements recorded twice on the healthy ear and twice on the affected ear:
  - Electrocochleography (EcoG)
  - Ocular and cervical VEMP
  - Wideband tympanometry (WBT)

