**9.4. FOLLOW-UP VISITS**

**Visit 2 (15 days ± 5 days)**
During visit 2, performed on site by study staff:

- Clinical examination and evaluation of cardinal symptoms
- Naert questionnaire
- Electrophysiological measurements recorded twice on the healthy ear and twice on the affected ear:
  - Electrocochleography (EcoG)
  - Ocular and cervical VEMP
  - Wideband tympanometry (WBT)

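### Section 7.4 sets blinding aside, and no other section keeps the examiner who reads EcoG and PEMV from knowing the symptom scores or the earlier readings

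*Protocol*

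**What the plan says.** - **Blinding.** Section 7.4 contains only "Not applicable".
- **Who tests.** Section 4.2.1.1 (EcoG) states "All recordings are performed by the same examiner within one center". Sections 4.2.1.2 and 4.2.1.3 repeat this for wideband tympanometry (WBT) and PEMV. Section 4.3.2 adds: "A trained operator (same in each center) will perform all electrophysiological tests using standardized equipment identical across visits".
- **What is tested.** Section 9.3.2: "Electrophysiological measurements recorded twice on the healthy ear and twice on the affected ear". Sections 9.4 and 9.5 ask for the same at visits 2 and 3, so each ear has six readings and its status is known when it is tested.
- **What else happens at those visits.** Section 9.4 opens with "During visit 2, performed on site by study staff" and lists "Clinical examination and evaluation of cardinal symptoms", the symptom questionnaire and the electrophysiology together. Section 9.5 does the same for visit 3. Section 9.3.2 assigns the inclusion visit to the investigator. None of the three sections fixes the order of procedures or says who collects the VAS scores.
- **How PEMV is read.** Section 4.2.1.3 records "wave amplitude characterization relative to the contralateral healthy side (absent, normal, or abnormally large". Section 2.1.2.1 concedes: "No standardized thresholds exist".
- **What counts as proof.** Section 4.3.1 expects SP/AP to correlate with each symptom VAS on the affected side, expects no correlation on the healthy side, and expects SP/AP to correlate more strongly than PEMV. Section 11.2 judges reliability first and averages the repeated readings if it is adequate.

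**The concern.** With no treatment arms, the masking that matters is between whoever reads the test and the symptom score the test is meant to track. The protocol provides none, and two separate biases follow.

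1. **Knowledge of the symptom scores.** An examiner who knows that a patient is badly affected, and which ear is dehiscent, can read that ear's trace accordingly. The affected-side correlation rises and the healthy side stays near zero. For SP/AP this is the convergent and divergent pattern that section 4.3.1 takes as evidence of validity. For PEMV it raises a correlation that section 2.2 expects to be weak or absent, and so distorts the planned comparison of SP/AP with PEMV.
2. **Knowledge of the earlier reading.** A second reading pulled towards the first raises the ICC and narrows the Bland-Altman limits. Because reliability is judged first, this also eases the decision to average the six readings.

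Who sees what when a trace is read is a matter of study conduct. A statistical analysis plan could not supply it later.

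**Working it through.** **The plan's own precision (section 11.1).** Fisher z at n=100: limits tanh(atanh(r) ± 1.96/√97).
- r=0: ±0.196, width 0.393. Stated: below 0.40. Reproduced.
- r=0.50: 0.337 to 0.634, width 0.298. Stated: below 0.30. Reproduced.
- ICC with six readings: width 0.102 (Bonett) or 0.101 (exact F) at exactly 0.80, and 0.098 or 0.097 at 0.81. The stated width below 0.10 for an ICC above 0.80 therefore holds from just above 0.80.

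These widths cover sampling error only. Masking changes none of them; it acts on bias.

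**Correlation bias.** The documents give no bias size, so b is an assumption: the shift in a reading, in SD, per SD of VAS. With true correlation r, the observed value is (r + b)/√(1 + 2rb + b²).

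| b | true r = 0 | true r = 0.30 |
|---|---|---|
| 0 | 0 | 0.30 |
| 0.1 | 0.1/√1.01 = 0.10 | 0.4/√1.07 = 0.39 |
| 0.2 | 0.2/√1.04 = 0.196 | 0.5/√1.16 = 0.46 |

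The two-sided 5% limit for a Pearson r at n=100 is 0.197. With no true association, the chance of a significant positive result is about 1 − Φ(1.96 − atanh(r)·√97). That is about 16% at b=0.1 and 50% at b=0.2, against a nominal 2.5%. A simulation of 200,000 patients with six averaged readings and a true ICC of 0.80 gives slightly more: 0.11 and 0.21 from a true r of 0. Averaging removes random error but leaves the bias.

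**Reliability bias.** Assume each later reading is pulled towards the one before by weight w. The same simulation gives:

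| w | true ICC 0.60 | true ICC 0.80 |
|---|---|---|
| 0 | 0.60 | 0.80 |
| 0.2 | 0.70 | 0.86 |
| 0.3 | 0.75 | 0.88 |
| 0.5 | 0.83 | 0.93 |

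This anchoring leaves the correlation essentially unchanged (with a true r of 0.30, between 0.28 and 0.30 for every w), so the two mechanisms are distinct and need separate safeguards.

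**Which readings are exposed.** The PEMV amplitude class is a three-way call against the other ear, and the protocol itself says that standardized thresholds are lacking, so judgement is documented there. For SP/AP, section 4.2.1.1 says that both potentials are recorded and the ratio calculated, but not whether the peaks are marked by hand or by software. The tables apply to SP/AP only to the extent that marking is manual.

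**The case against.** Section 7.4 sits in the chapter on study treatment, beside comparator and product-circuit sections that are also marked as not applying, and section 5.3 says there is no randomisation. Read as treatment blinding, the entry is correct. A dedicated trained examiner per centre suggests some division of labour, and no section says that this person collects or sees the VAS. Training and common equipment are specified. This much stands: the fault is an omission of assessor masking, not a false statement. But training and equipment limit random variation; they do not stop an examiner from knowing a score or an earlier value.

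A reader might infer more than the documents support:
- *That symptoms are always scored first, by the person who then tests.* Sections 9.3.2 to 9.5 are unordered lists and do not name who collects the scores.
- *That the primary correlation will be inflated.* Judgement in marking SP/AP is an assumption.
- *That every reading bias favours the hypotheses.* For PEMV it works against them, because it narrows the expected gap to SP/AP.
- *That knowing the side is enough.* A uniform shift of all affected-ear readings leaves the within-side r unchanged; side matters only together with the scores.
- *That the damage could never be undone.* Masked re-reading would remain possible if raw traces were kept, although section 12.1 lists only reports of recordings among the source documents.

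**Conclusion.** The concern holds as an avoidable gap in study conduct. The protocol leaves open that the examiner knows symptom scores and earlier readings, in a study whose evidence is a one-sided correlation and a reliability check made by the same hands. Exposure is documented for the PEMV amplitude class, and hence for the SP/AP versus PEMV comparison. For SP/AP it is possible but unquantified. If readings did shift by 0.2 SD per SD of VAS, the spurious correlation of 0.196 would equal the whole half-width that section 11.1 allows at r=0. If marking is automatic, the shift for SP/AP could be close to nil. Both b and w are assumptions. This is worth correcting before recruitment because the core safeguard is nearly free. It does not invalidate the design.

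**What to change.** Replace the entry in section 7.4 with text to this effect:

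- Treatment blinding does not apply.
- Patients complete the VAS, the symptom questionnaire and the EQ-5D-5L themselves. The examiner does not see these scores, on paper or in the eCRF.
- The examiner does not consult earlier values when recording or marking a later measurement.
- Where traces can be exported, the same centre examiner marks SP/AP and the PEMV amplitude class on coded traces in random order, masked to identity, visit and replicate. For PEMV the two ears of a patient stay together as an unlabelled pair, because the class needs the contralateral comparison.

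PEMV thresholds determined live are protected only by withholding the scores and earlier values.

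**Cost.** Withholding scores and earlier values needs an eCRF access setting and a short instruction. Coded reading is more work: EcoG alone gives 100 patients × 2 ears × 6 readings = 1,200 recordings, with ocular and cervical PEMV on top. It adds an export and relabelling step, and readings become available later. No extra patient, visit, test or reader is needed. If export is not feasible, withhold the scores and earlier values only, and state the remaining limitation in section 7.4.
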